#### Secondary outcomes

Data for the secondary and exploratory outcome measures will primarily be collected during the acute phase of disease, when patients are admitted to the PICU. Ventilator settings and respiratory system parameters will be read from the ventilator. Blood sampling will be done to assess pCO_2_ and pH; to calculate the PaO_2_/FiO_2_ ratio and the OI (calculated by [mean airway pressure * FiO_2_ * 100]/PaO_2_) the PaO_2_ needs to be determined in arterial blood samples. The SpO_2_/FiO_2_ ratio can be calculated if SpO_2_ < 98%. If no indwelling arterial line is present, the OSI  ([mean airway pressure * FiO_2_ * 100]/SpO_2_) is used. Haemodynamic parameters are read from the patient monitor; cumulative fluid balance is calculated as the sum of daily fluid balance; it is normalised to actual bodyweight. Calculation of the non-respiratory PELOD-2 requires the Glasgow Coma Score, pupillary reaction to light (both reactive/both dilated), lactate, mean blood pressure, creatinine, white blood cell count, and platelets. Blood sampling will be done using the indwelling arterial line or central venous line. The pRIFLE criteria require assessment of serum creatinine and urine output as described elsewhere [28].

Published criteria are used to study the prevalence of critical illness polyneuropathy and myopathy (CIPNM) [19, 31]. The diagnosis CIPNM is present if the patient has possible limb weakness (i.e. inability to raise the limbs against gravity upon a stimulus), electrophysiological evidence of axonal motor and sensor polyneuropathy, and if the patient is difficult to wean from the ventilator and no apparent cause is present. Strength of muscle limbs will be assessed daily by the attending physician as part of the routine clinical examination after 48 h after randomisation until the moment of discharge from the PICU. If this is present and the patient cannot be weaned of the ventilator, a paediatric neurologist is asked for consultation and electromyographic investigations are indicated. The latter two are part of routine care in patients with unexpected muscular weakness. Only then the diagnosis of CIPNM is confirmed or refuted. Centre for Disease Control definitions for ventilator-associated pneumonia (VAP) will be used [32]. Both CIPNM and VAP will be assessed daily by the attending physician as part of the routine clinical examination 48 h after randomisation until the moment of discharge from the PICU.

Assessment of the level and time course of the cumulative respiratory morbidity score assessed at baseline, 3, 6 and 9 months after PICU discharge will be done using the same questionnaire as described above. LCI and FRC will be measured 12 months after PICU discharge using multiple breath washout techniques [33]. Such lung function testing is feasible and validated, even in small children. Testing will be performed by dedicated paediatric pulmonology function testing technicians in participating centres that are equipped with this technique.

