**Methods:**

This is a phase IV, multicentre, randomised, double-blind, placebo-controlled trial performed in level-3 PICUs in the Netherlands. Eligible for inclusion are children younger than 5 years of age requiring invasive mechanical ventilation with positive end-expiratory pressure (PEEP) ≥ 5 cm H_2_O for moderate-to-severe PARDS occurring within the first 96 h of PICU admission. Patients are randomised to continuous infusion of rocuronium bromide or placebo for 48 h. The primary endpoint is the cumulative respiratory morbidity score 12 months after PICU discharge, adjusted for confounding by age, gestational age, family history of asthma and/or allergy, season in which questionnaire was filled out, day-care and parental smoking. Secondary outcomes include respiratory mechanics, oxygenation and ventilation metrics, pulmonary and systemic inflammation markers, prevalence of critical illness polyneuropathy and myopathy and metrics for patient outcome including ventilator free days at day 28, length of PICU and hospital stay, and mortality

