### Objectives {7}

The primary objective is to test the hypothesis that the use of NMBAs for 48 h in paediatric patients younger than 5 years of age with early moderate-to-severe PARDS will lead to at least a 20% reduction in cumulative respiratory morbidity score 12 months after discharge from the PICU.

The secondary objectives are to evaluate the effects of NMBAs on pulmonary and systemic inflammation, metrics for oxygenation and ventilation, non-respiratory organ dysfunction, and respiratory system mechanics.

Exploratory objectives: ventilator free days (VFD) at day 28, PICU and hospital length of stay, 90-day mortality, concomitant use of sedatives, complications (e.g. adverse drug reactions, reintubation rate, critical illness polyneuropathy and myopathy, ventilator-associated pneumonia (VAP), withdrawal syndrome, delirium), the course of the respiratory morbidity score at 3, 6 and 9 months and lung function (lung clearance index (LCI), functional residual capacity (FRC).

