Patients will be managed using a conservative fluid strategy. The goal is adequate cardiac output to meet the metabolic needs of the patient, specifically, a normal blood pressure for age, brisk capillary refill, and adequate peripheral perfusion to achieve adequate end organ perfusion. The care team will delineate daily mean arterial blood pressure goals. Hemodynamic management may be guided by devices such as pulse contour cardiac output (PiCCO). Diuretic therapy is used to achieve desired fluid balance. Type of drug, starting and maintenance dose is at the discretion of the local care team, taking the goals of fluid management into account. Use of vaso-active medications is also at the discretion of the care team. Maintenance fluids are calculated per standard paediatric practice according to local guidelines. The care team will determine the type of fluid (colloids, crystalloids) administered. All fluids, including IV continuous infusions, IV intermittent medications, blood products, IV and enteral nutrition, will contribute to the patient’s hourly total. Medications should be administered using the least amount of fluid possible.

Patient’s level of comfort is assessed per phase of illness and criticality at least every 4 h while intubated. The Comfort B score is used per discretion of the local care team in all patients, although it must be noted that it cannot be used in paralysed patients [26]. In all patients, patient comfort is also deemed insufficient if there is a persistent > 20% increase in heart rate and blood pressure either spontaneously or with stimulation despite managing obvious causes for discomfort such as (partial) endotracheal tube blockage, mucus retention or constipation. If present, sedation and/or analgesia regimens can be modified according to local guidelines. Centres may substitute drugs within a class (e.g. narcotics - morphine or fentanyl or benzodiazepines - midazolam and lorazepam) and by route of administration (e.g. enteral for intravenous). Alternative measures such as the analgesia nociception index (ANI) require additional monitoring devices that are not available in all participating centres. Local screening tools for withdrawal and/or delirium will be used.

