#### Secondary outcome measures

Secondary outcomes include LCI and FRC measured using multiple breath wash-out 12 months after PICU discharge, and the level and time course of the cumulative respiratory morbidity score assessed at baseline, 3, 6 and 9 months after PICU discharge. Secondary outcome measures related to the acute phase of disease (i.e., during PICU admission) include level and time course of ventilator settings (peak inspiratory pressure, plateau pressure, mean airway pressure, driving pressure, PEEP, set rate, total rate, inspiratory time), respiratory system mechanics (quasistatic compliance, dynamic compliance, respiratory system resistance), metrics of oxygenation (SpO_2_/FiO_2_ ratio, PaO_2_/FiO_2_ ratio, OI, OSI) and ventilation (PCO_2_, pH), and hemodynamic parameters (heart rate, blood pressure, central venous pressure, daily cumulative fluid balance, number of fluid challenges). We will measure the level and time course of the non-respiratory pediatric logistic organ dysfunction 2 (PELOD – 2) score as measure of organ dysfunction and pediatric Risk, Injury, Failure, End-stage renal failure (pRIFLE) criteria for acute kidney injury, the number of adverse drug reactions, and re-intubations [27, 28]. We will study the level and time course of the pulmonary and systemic inflammatory response, the prevalence of critical illness polyneuropathy and myopathy, and ventilator-associated pneumonia.

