### Participant timeline {13}

A schema of this trial and a timeline is presented in the SPIRIT figure below (see Table 1). The total study duration will be the length of PICU admission plus 12 months follow-up. Patients receive the intervention during the first 48 h after enrolment.

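### The non-respiratory PELOD-2 includes the Glasgow Coma Score, which paralysis makes unreadable in one arm, so the score may differ by arm during the infusion without a true difference in organ dysfunction

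*Protocol article*

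**What the plan says.** The Objectives section names "non-respiratory organ dysfunction, and respiratory system mechanics" among the things on which the effect of blockade is to be evaluated. Under Secondary outcome measures the protocol states: "We will measure the level and time course of the non-respiratory pediatric logistic organ dysfunction 2 (PELOD – 2) score as measure of organ dysfunction". The score is listed with the outcomes of the acute phase, that is, those collected during PICU admission. The Secondary outcomes part of Plans for assessment and collection of outcomes {18a} fixes its inputs: "Calculation of the non-respiratory PELOD-2 requires the Glasgow Coma Score, pupillary reaction to light", followed by lactate, blood pressure, creatinine, white cells and platelets.

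On treatment, the Abstract says "Patients are randomised to continuous infusion of rocuronium bromide or placebo for 48 h", and Participant timeline {13} says "Patients receive the intervention during the first 48 h after enrolment". Who will be blinded {17a} accepts that children in the control arm may move or breathe on their own.

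On analysis, the Statistical methods section plans generalised estimating equations for repeated secondary outcomes, with arm, time and any applicable confounders. It sets aside no component of the score and no time window.

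Paralysis is taken into account for two other measures. For the Comfort B score the protocol adds "although it must be noted that it cannot be used in paralysed patients". Daily limb-strength examination begins only once 48 h have passed since randomisation.

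**The concern.** The coma item is built from a child's observable responses. A neuromuscular blocker removes movement whatever the state of the brain. For as long as the drug acts, a poor coma value in the rocuronium arm says nothing about neurological dysfunction, whereas a value in the placebo arm still says something.

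The assigned treatment thus acts on the measurement itself, in one arm. Neither randomisation nor covariate adjustment removes such a distortion, because it arises after randomisation and is caused by the treatment.

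The outcome serves a stated secondary objective. If observed responses are scored, the distortion runs towards worse apparent organ dysfunction under rocuronium. It could then suggest harm, or hide a benefit of the kind that the Background reports from adult studies. If the item is instead left blank in paralysed children, missingness depends on arm.

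**Working it through.** The protocol states no figure on this point, so there is none to reproduce. The check has two parts.

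**Reading the sections together**

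1. Required input: the coma score, under Secondary outcomes in {18a}.
2. Period of measurement: the PICU stay, under Secondary outcome measures.
3. Period of paralysis: the first 48 h after enrolment, in one arm, under Participant timeline {13}. This lies inside the period in step 2.
4. Contrast between arms: control children may move, under {17a}. Against this, Adverse event reporting and harms {22} says that children with severe lung injury are usually under deep sedation, which applies to both arms.
5. Comparison: by arm and time, with nothing excluded, under Statistical methods.
6. Protection against paralysis: present for Comfort B and for limb strength, absent for the coma item.

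Steps 1 to 5 are enough for a difference between arms that treatment causes through measurement alone. Step 6 shows that the protocol recognised the difficulty elsewhere.

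**How large it could be (illustration, assumed inputs)**

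Let w be the amount, in standard deviations (SD) of the total score, that is added when the coma item is scored at its worst level. Let f be the share of control children who are also at that level. Assume that every rocuronium child is scored there and that there is no true effect. The false shift is

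shift = w × (1 − f).

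For n children per group, the standard error in SD units is √(2/n). The chance of a significant difference at one time point, two-sided 5%, is

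Φ(shift/SE − 1.96) + Φ(−shift/SE − 1.96).

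The protocol gives n = 89 per group and alpha 5%. The two-sided test, w and f are assumptions. SE = √(2/89) = 0.150.

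| f | shift, w = 0.5 | chance | shift, w = 1.0 | chance |
|---|---|---|---|---|
| 0 | 0.50 | 91.6% | 1.00 | about 100% |
| 0.5 | 0.25 | 38.5% | 0.50 | 91.6% |
| 0.8 | 0.10 | 10.2% | 0.20 | 26.6% |
| 0.9 | 0.05 | 6.3% | 0.10 | 10.2% |
| 1.0 | 0 | 5.0% | 0 | 5.0% |

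Example: w = 1.0 and f = 0.8 give 1.0 × 0.2 = 0.20 SD. Then 0.20/0.150 = 1.33, and Φ(1.33 − 1.96) is about 0.266; the other tail is negligible.

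With n = 74 per group, shifts of 0.10, 0.25 and 0.50 SD give 9.3%, 33.0% and 86.0%.

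The result runs from no effect to a decisive one. The protocol article fixes neither of the two things that decide it: how the item is scored under paralysis, and how responsive sedated controls are.

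**The case against.** The strongest objection is that this is a scoring detail. The article only lists the inputs to the score. It cites published sources for PELOD-2 and pRIFLE, and it condenses a full protocol that is not shown. A rule for children who are sedated or paralysed may stand in that protocol, in an analysis plan or in the cited definition. A rule that omits the item or carries an earlier value in both arms would remove the artefact. This stands as a limit on what can be concluded. It does not dispose of the point, because the article itself names the coma score as required, compares the score across the infusion period without exception, and allows for paralysis in two neighbouring measures.

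A second objection is that the contrast between arms may be small. Every child is invasively ventilated, so a normal verbal response is unavailable in either arm, and deep sedation lowers eye and motor responses in controls too. This also stands. If all controls were at the worst level, the artefact would be zero. The protocol nevertheless expects that some controls may move.

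A third objection is that the assessment schedule (Table 1) is not visible, so it cannot be shown how many assessments fall within the 48 h. That is correct, and it is a reason to call the effect possible and not established.

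A reader might infer that the score will differ by arm, or might put a definite number of points on the difference. The documents support neither. They do not say that paralysed children are scored at the worst level, and they give no weight for the item and no figure for control responsiveness.

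**Conclusion.** The point holds as a risk. As defined in the article, the non-respiratory PELOD-2 is open to a difference between arms during the infusion that reflects paralysis and not organ dysfunction, and no stated rule prevents it.

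Its size is unknown. It is zero if sedated controls are as unresponsive as paralysed children, or if one neutral scoring rule is used in both arms. It is material if observed values are scored and controls respond more. The percentages in the table rest on assumed values of w and f and only show how wide that range is.

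Severity is low. One component of one secondary outcome is affected, for about the first 48 h plus any residual drug effect. It would be going too far to infer that the organ dysfunction outcome is invalid over the whole PICU stay, or that the trial's main result is in doubt. Later assessments are open to this problem only through residual effects, and the 12-month respiratory morbidity score does not use the coma item.

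**What to change.** State one rule before unblinding. From randomisation until the infusion has ended and its effect has worn off, compare the arms on the non-respiratory PELOD-2 without the coma item, identically in both arms. Use the full score only after that window.

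Two details make the rule work:

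- Define the end of the window as a fixed time from randomisation, the same for both arms and set in advance by the trial team. A window that ends when a child is seen to recover movement would itself differ by arm.
- The score with and without the coma item is on different scales, so do not join the two into one trajectory.

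Carrying forward a coma score from before sedation is not recommended unless such a score is recorded. The article does not say that it is, and because PARDS may arise up to 96 h after PICU admission, a child may already be intubated and sedated by then.

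The cost is small: the rule needs no new data. The downside is that the coma item contributes nothing in the first days, so a true early neurological difference would not show in this outcome. If the full protocol or analysis plan already holds an arm-neutral rule, a cross-reference to it is enough.

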### Interim analyses {21b}

The data safety monitoring board (DSMB) will monitor the study for efficacy and adverse events. Two interim analyses are planned after the inclusion of 50 and 100 patients respectively. For safety reasons, the study will be terminated prematurely if there is a significant increase in critical illness polyneuropathy and myopathy in these interim analyses (i.e. a threefold increase in prevalence) or for futility if there is no difference in the primary outcome measure.

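### The written CIPNM case definition has no place for isolated myopathy and requires difficult weaning, so the only named safety stopping outcome will undercount the harm it is meant to detect

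*Protocol article*

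**What the plan says.** All of the definition stands in the Protocol article, Plans for assessment and collection of outcomes {18a}, under Secondary outcomes. The outcome is named as critical illness polyneuropathy and myopathy, and published criteria are cited for it. The rule is then written out. Its first element is limb weakness: "The diagnosis CIPNM is present if the patient has possible limb weakness (i.e. inability to raise the limbs against gravity upon a stimulus". To this are joined "electrophysiological evidence of axonal motor and sensor polyneuropathy, and if the patient is difficult to wean from the ventilator"; the weaning difficulty must also lack an apparent cause.

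The route to confirmation follows: "If this is present and the patient cannot be weaned of the ventilator, a paediatric neurologist is asked for consultation and electromyographic investigations are indicated". It is added that "Only then the diagnosis of CIPNM is confirmed or refuted". The article also describes the consultation and the electromyography as part of routine care for unexpected muscular weakness.

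On timing: "Strength of muscle limbs will be assessed daily by the attending physician as part of the routine clinical examination after 48 h after randomisation", continuing until PICU discharge. The study infusion lasts 48 h, and Participant timeline {13} says: "Patients receive the intervention during the first 48 h after enrolment".

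Interim analyses {21b} gives the outcome its weight. After 50 and 100 inclusions, "the study will be terminated prematurely if there is a significant increase in critical illness polyneuropathy and myopathy", with the increase described as threefold. No other safety criterion for stopping is named there.

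**The concern.** The name of the outcome has two parts, but the definition tests for one. The only electrophysiological finding that qualifies is an axonal polyneuropathy, and it is a required condition. A child whose electromyography shows myopathy alone does not meet the rule.

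The weaning condition narrows it again. Strength is examined every day until PICU discharge, so also after extubation, but weakness first noticed in a child who came off the ventilator without difficulty has no way to become a case. The diagnostic criterion and the trigger for the work-up are also worded differently: the first asks for difficulty in weaning, the second for inability to wean.

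The article presents CIPNM as the most prominent side effect to be weighed against benefit (Discussion), and it names muscular weakness after prolonged rocuronium infusion as a risk in its own right (Intervention description {11a}). Yet the adverse events listed under {22} include CIPNM and no separate item for limb weakness. Children who fall outside the definition could surface only through the investigator-judged category of clinically relevant incidents.

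A secondary matter is the clock. The strength checks are timed from randomisation and not from the end of the infusion.

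**Working it through.** **1. The criteria applied to four kinds of weak child.** All have limb weakness, and weaning difficulty, where present, has no apparent cause.

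| Child | Axonal polyneuropathy | Difficult to wean | Case under the written rule? |
|---|---|---|---|
| A | yes | yes | yes |
| B: isolated myopathy | no | yes | no |
| C: weaned without difficulty | yes, if tested | no | no |
| D: difficult to wean, later extubated | yes | yes | yes |

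B is excluded by the electrophysiological condition and C by the weaning condition. D shows that extubation in itself does not exclude a child.

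**2. The one prevalence figure in the document.** Intervention description {11a} cites 55 cases of ICU-acquired weakness in 203,875 admissions: 55/203,875 = 0.027%, which rounds to the stated 0.03%. At that rate 100 patients yield 100 × 0.00027 = 0.03 expected cases. The figure describes all PICU admissions, not ventilated children with moderate-to-severe PARDS, so the trial's rate may be higher. The document does not give it.

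**3. What equal undercounting does to the threefold rule.** Let s be the share of true cases that the definition counts, equal in both arms. The recorded rates are s·p1 and s·p2, and their ratio s·p2/(s·p1) = p2/p1 does not change. Precision does. Assume true rates p1 = 5% and p2 = 15%, a two-sided 5% test, and looks at 50 and 100 patients, that is 25 and 50 per arm. The normal approximation is

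power = Φ{[Δ − 1.96·√(2p̄(1−p̄)/n)] / √([p1(1−p1)+p2(1−p2)]/n)},

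with the recorded rates put in, Δ their difference and p̄ their mean. For s = 1 and n = 50: (0.10 − 1.96 × 0.0600)/0.0592 = −0.297, so power is 38%.

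| Share counted, s | Expected cases, 25 per arm | Power | Expected cases, 50 per arm | Power |
|---|---|---|---|---|
| 1 | 1.25 v 3.75 | 21% | 2.5 v 7.5 | 38% |
| 0.5 | 0.63 v 1.88 | 12% | 1.25 v 3.75 | 21% |
| 0.25 | 0.31 v 0.94 | 8% | 0.63 v 1.88 | 12% |

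With counts this small the approximation is rough, and both the rates and s are assumptions. The table shows direction and order of size only.

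**4. Timing.** If the infusion starts t hours after randomisation, it ends at 48 + t. For assumed t = 0, 1, 2 and 4 h it ends at 48, 49, 50 and 52 h. The check window opens at 48 h, so it opens at the end of the infusion (t = 0) or before it (t > 0). The article states no interval after the infusion and no check for residual block. The first actual daily check may fall up to about a day after the window opens.

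**The case against.** The strongest defence has four parts.

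First, the article relies on published criteria that are not at hand. They may treat myopathy properly, and the sentence may be a condensed paraphrase. That cannot be ruled out. Still, the article spells out when the diagnosis is present, and the rule as printed contradicts the outcome's name.

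Second, the stopping rule is a ratio, which equal undercounting leaves unchanged, and at the cited 0.03% rarity limits the rule far more than the definition does. Both points stand. They bound the harm: what is lost is events, in a rule that has few to spare.

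Third, a reader might infer that the early strength checks bias the comparison against rocuronium, or that children are known to be examined while still paralysed. The documents do not support either. The hour of the first check, the start delay and the time to recovery are not given. Checks repeat daily. Weakness alone does not open the work-up, which also needs inability to wean, and it cannot count as a case without axonal polyneuropathy and weaning difficulty without apparent cause. What remains is a missing interval, with an attending physician as assessor whose full blinding the article says cannot be ensured.

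Fourth, a reader might infer that no extubated child can ever be tested or counted. That is also too strong. A child who was difficult to wean and was extubated later can meet the criterion, and electromyography is described as routine care for unexpected weakness. The exclusion applies to the child who weaned without difficulty.

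**Conclusion.** The definition and the name of the outcome do not match, and the mismatch should be fixed. Isolated myopathy cannot be counted under the written rule, nor can weakness first seen in a child who weaned without difficulty. The criterion and the work-up trigger also disagree on weaning. This rests on the printed text alone and needs no assumption.

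The consequence is lost sensitivity to a threefold increase, not a demonstrated bias. Its size is unknown, because the document gives neither the share of myopathy nor the CIPNM rate expected in this population. Under the assumed rates of 5% and 15%, counting half of the cases roughly halves power at either look. If the loss differed between arms, the ratio would shift too, but nothing in the document shows that it would.

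The timing point is secondary: no interval separates the end of the infusion from the start of the strength checks, so early readings may coincide with residual block.

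**What to change.** Under {18a}, Secondary outcomes:

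1. Reconcile the outcome's name, its criteria and the work-up trigger. Let the electrophysiological criterion cover polyneuropathy and/or myopathy, and word the weaning condition the same way in the diagnosis and in the trigger. Which children are clinically investigated is for the investigators to settle; the passages only need to agree.
2. Report limb weakness from the existing daily examination to the DSMB, by arm, as a separate safety outcome, whether or not weaning is difficult. This captures the children whom a weaning condition would still leave out of confirmed CIPNM.
3. For that outcome, count weakness from the end of the study infusion in both arms, and require it to persist on consecutive daily checks, so that residual block is not recorded as weakness.

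The cost is an amendment to an outcome definition and a changed time anchor on the case report form. The daily examination, the consultation and the electromyography are already described as routine care, so no visit or procedure is added. Recorded rates may be higher in both arms, and the first counted reading will come slightly later. As the trial is already enrolling, the same definition should be applied to children already included as far as their recorded findings allow.

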### Who will take informed consent? {26a}

Site investigators will screen for eligible subjects daily. Screening logs will be used to facilitate the screening process and provide an auditable record of potentially eligible subjects. Parents or legal caretakers are informed by a member of the study team about the study as soon as possible when a patient becomes eligible for inclusion. The study team will explain the study to the parents and ask for informed consent. Parents/legal caretakers will have 12 h to consider giving consent, provided that this period does not exceed the 96-h interval between time of PICU admission and study enrolment. At least one parent/legal caretaker must give written consent while the other can give verbal consent to include the subject, hereafter written consent will be gained within 48 h after inclusion.

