### Adverse event reporting and harms {22}

For this study, the following adverse events (AE) are defined pneumothorax, decubitus, CIPNM, VAP, withdrawal syndrome, delirium, hypotension or tachycardia in response to study medication with need for intervention by means of medication or fluid challenge, allergic reaction and reintubation. These AEs will be recorded in the database. A serious adverse event (SAE) is any untoward medical occurrence or effect that cannot be attributed to the underlying disease or that can be expected in the natural disease course of paediatric acute respiratory distress syndrome. For this study, the following SAEs are defined death (all-cause mortality), hypersensitivity or an allergic reaction that is not attributable to any concurrent medication, defined by skin rash and/or hypotension and/or severe bronchospasm necessitating the use anti-histaminic drugs and corticosteroids and/or vasopressors, cardiac arrhythmias or dysrhythmias and clinically relevant incidents, judged by the investigator, which are unexpected within the natural course of PARDS. An elective hospital admission will not be considered as a serious adverse event.

The risks associated with this study are minimal based on the following arguments
Patients in the intensive care unit are under constant tight observation, so any change in vital parameters is noted immediately. Furthermore, patients with severe lung injury are commonly deeply sedatedBlood samples are only taken from an indwelling arterial catheter or central venous catheter, which are already in place for clinical purposes. Blood samples for this study will be combined as much as possible with routine blood sampling part of daily clinical careEndotracheal suctioning is routinely performed in mechanically ventilated patients by nurses taking care of the patients; for this study suctioning specimens are collected to measure the pulmonary inflammatory responseThe investigational drug is commonly used in (paediatric) critical care; hence, there is a good understanding of this drug.

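### The scheduled VAP assessment opens only 48 h after randomisation, so almost none of the study-drug infusion is covered for the secondary outcome, and this does not match the open-ended adverse-event recording of VAP

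*Protocol article*

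**What the plan says.** Under Plans for assessment and collection of outcomes {18a}, Secondary outcomes, the protocol article gives critical illness polyneuropathy and myopathy (CIPNM) and VAP one shared window: "Both CIPNM and VAP will be assessed daily by the attending physician as part of the routine clinical examination 48 h after randomisation until" the child leaves the PICU. The same paragraph starts the daily limb-strength examination at the same time. For the case definition it says: "Centre for Disease Control definitions for ventilator-associated pneumonia (VAP) will be used".

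The abstract gives the treatment period: "Patients are randomised to continuous infusion of rocuronium bromide or placebo for 48 h". Participant timeline {13} places it: "Patients receive the intervention during the first 48 h after enrolment".

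VAP has two roles. Secondary outcome measures lists "the prevalence of critical illness polyneuropathy and myopathy, and ventilator-associated pneumonia". Adverse event reporting and harms {22} says that "the following adverse events (AE) are defined pneumothorax, decubitus, CIPNM, VAP, withdrawal syndrome, delirium" and others, and adds: "These AEs will be recorded in the database". That section gives no start time and no assessment schedule for VAP.

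**The concern.** A delay of 48 h makes sense for CIPNM, because limb strength cannot be judged in a paralysed child. Pneumonia can be looked for during paralysis, and the article gives no separate reason for delaying its assessment. Nor can the delay stand in for a minimum time on the ventilator, because it runs from randomisation and not from intubation.

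The first 48 h are the only period in which the arms differ in study treatment. They are also a period in which most participants should be ventilated and at risk, since Eligibility criteria {10} excludes children expected to be ventilated for less than 48 h.

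At stake is the quality of a between-arm safety comparison. The trial could report VAP by arm with almost no scheduled assessment during treatment. Any earlier case would then reach the database only through unscheduled adverse-event reporting. Who will be blinded {17a} concedes that the clinical team may be able to tell the arms apart, so the completeness of that reporting could differ by arm.

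**Working it through.** The article states no figure for this point, so there is none to reproduce. The check compares two time intervals.

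**Inputs**
- VAP assessment window: from 48 h after randomisation to PICU discharge (section {18a}).
- Infusion: 48 h long, in the first 48 h after enrolment (abstract; section {13}).
- Lag L from randomisation to infusion start: not stated, so treated as an assumption.
- Ventilation time after randomisation, D days: not stated, so treated as an assumption.

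**Step 1: overlap of infusion and window.** The infusion runs from L to L + 48 h and the window opens at 48 h. The overlap is (L + 48) − 48 = L hours, or L/48 of the infusion.

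| Assumed lag L | Infusion inside the window | Infusion before the window |
|---|---|---|
| 0 h | 0 h (0%) | 100% |
| 1 h | 1 h (2%) | 98% |
| 6 h | 6 h (12.5%) | 87.5% |
| 12 h | 12 h (25%) | 75% |

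With a prompt start, almost the whole infusion precedes the first scheduled VAP assessment.

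**Step 2: share of at-risk time before the window.** Assume a constant daily hazard of VAP and ventilation for D days after randomisation. The first 2 days then hold 2/D of the onset time.

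| Assumed D | 2/D |
|---|---|
| 3 days | 67% |
| 5 days | 40% |
| 7 days | 29% |
| 10 days | 20% |
| 14 days | 14% |

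This is a share of onset time and not of missed cases. An episode that begins during the infusion and is still present, or first becomes diagnosable, after 48 h can be found then. So 2/D is an upper bound on the share that the secondary outcome could miss.

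**Step 3: does the delay represent ventilation time?** The consent section {26a} allows the parents' reflection period "provided that this period does not exceed the 96-h interval between time of PICU admission and study enrolment". Take a child intubated on admission and randomised at hour 96. The unscheduled period is hours 96 to 144 of ventilation, that is, ventilator days 5 and 6. For a child intubated shortly before randomisation it is days 1 and 2. One fixed delay therefore covers very different stages of ventilation. The first example is at the edge of eligibility and serves only to show this.

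**Step 4: the two roles side by side.** Section {18a} fixes a start at 48 h for the outcome. Section {22} records VAP as an adverse event with no start. Either adverse-event recording follows the 48 h schedule, and the infusion has no scheduled ascertainment for either purpose; or it covers 0–48 h without a schedule, and the two counts use different windows. The article does not say which.

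**The case against.** A reader might infer that pneumonia arising during paralysis is not counted, and that an excess would be absent from the data safety monitoring board's tables. The document supports neither inference. No section excludes VAP by onset date: section {18a} sets when daily assessment starts, the outcome is a prevalence, and an episode still present at 48 h can be detected and counted. Section {22} has VAP recorded as an adverse event without a time limit, Interim analyses {21b} has the board monitor adverse events, and patients are described as closely observed throughout. All of this stands, and it confines the point to scheduled assessment and to the mismatch between the two windows.

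It can also be said that few episodes will begin and resolve within 48 h, that the window is the same in both arms, that no direction of bias has been shown, that some early cases will have been incubating at randomisation, and that pneumonia due to paralysis may present after it ends. These are fair and limit the likely size. They do not supply a reason for leaving the treatment period without scheduled assessment. An identical window does not protect the comparison if early reporting differs by arm.

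Finally, the text of the cited VAP definition is not in the article, so whether it restricts early diagnosis or dates onset retrospectively cannot be judged here. Details of the case report form may well be in the full protocol. The start of the window, however, is fixed in this article.

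**Conclusion.** The point holds as a matter of ascertainment and consistency. For the secondary outcome, scheduled VAP assessment covers none of the infusion if study drug starts at randomisation, and 2–12.5% of it for an assumed lag of 1–6 h. The outcome window and the adverse-event recording do not match as written.

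The cases at risk of being missed by the secondary outcome are episodes that resolve before 48 h and episodes in children who die or leave the PICU before 48 h. Others can be found later, possibly with a wrong onset date; that does not alter a simple prevalence but would blur any split by period. The ceiling of 20–40% rests on an assumed 5–10 ventilator days after randomisation and a constant hazard. The true loss is probably smaller, and the article gives no VAP rate from which to estimate it.

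VAP is a secondary and safety outcome and is in no stopping rule. The primary analysis is unaffected. The change is worth making because it is cheap and improves safety ascertainment during treatment.

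**What to change.** - In section {18a}, separate the two windows. Keep CIPNM from 48 h after randomisation, and assess VAP daily from randomisation to PICU discharge in both arms under the cited definition.
- Record the date of onset and whether VAP was already present at randomisation.
- Tabulate VAP with onset at 0–48 h and after 48 h separately by arm, and state that both count towards the secondary outcome.
- In section {22}, state that adverse-event recording of VAP uses the same start and the same definition.

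The cost is a sentence in each of two sections, two fields on the case report form, and two more days of an assessment already made in routine care. The article already assesses withdrawal and delirium daily without such a delay (Exploratory outcome measures under {18a}). The drawback is that some early cases may have been incubating at randomisation; the separate 0–48 h row makes these visible.
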